### Study size

A total of 500 patients are recruited for this study. With an expected 20% loss to follow-up, this results in a final sample size of 400, giving over 90% power to detect a 20% reduction in hospital admissions at a 5% significance level. This effect size is a rate ratio of 0.8 based on an average of 2.5 admissions per patient over a two year period in the control group, compared to 2.0 in the intervention group. The study has more than 80% power to detect a clinically significant difference in ED re-presentations, since ED presentations are more common than hospital admissions. A sample size of 400 would also allow us to detect a mean difference of 10 points on the EQ-5D scale [16], with approximately 80% power at a 5% significance level.

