### Consent and randomisation

Written informed consent is obtained from all patients. All patients identified by the inclusion screening process are either a) approached in person by a research officer or CN nurse to discuss study participation; or b) approached by telephone, if the patient is identified by the screening process out of hours. All patients approached by telephone are given a patient information sheet while in the hospital, and sign a ‘consent to approach’ form, giving permission for study staff to contact them by telephone.

Randomisation is 1:1 allocation and is conducted using permuted block design and stratified by age group (age ≥ 70, or age ≥ 45 for Aboriginal or Torres Strait islander patients). The randomisation is administered by an independent body (the NHMRC Clinical Trials Centre’s Randomisation Service), who are contacted by telephone for the allocation of each patient to a study arm. Allocation remains masked until after recruitment to the study. Once a participant is randomised, the research officer, the CN nurses and participant are not blinded. The research assistant collecting participant follow-up data remains blind to the treatment allocation throughout the two-year follow-up period. Study statisticians remain blind to allocation until after statistical analyses are complete.

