### Statistical analysis

Cox proportional hazards models are used to analyse time to first ED presentation, time to first readmission and time to mortality. Readmission rates and length of stay are analysed using Poisson or Negative Binomial models. EQ-5D is analysed using analysis of variance, and t-tests for pairwise comparisons. Baseline characteristics, such as age, gender and severity of illness are examined. Model checking of assumptions and good-of fit tests are conducted for all analyses and further analyses are conducted as required. All analyses are conducted according to the intention-to-treat principle, and will be conducted in SAS v9.3.

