## Discussion

To our knowledge, this is the first study to provide a mixed-method evaluation of the implementation and effectiveness of a care coordination program in Australia that includes a heterologous population and substantial follow-up period. Evidence of any improved patient outcomes and satisfaction due to care coordination are critical, given recent interest by governments. Coordinated care is becoming incorporated at the national policy level in several countries [11,12,17]. The integration and continuity of prevention and care is a priority action area in the National Chronic Disease Strategy of Australia [17]. These policy initiatives must be underscored by a solid evidence-base.

The main strengths of this study are the nature of the CN intervention, the comprehensive process evaluation, and the design of the RCT. The quantitative components of the study utilise a *pragmatic* RCT, allowing heterologous patient groups to be randomised to receive interventions that can be tailored to individual patients based on type, complexity and severity of disease, while still providing statistically meaningful information. The intervention identifies patients in the acute setting with a single point of access, involves GPs, builds capacity within the ED, and places the patient at the centre of decision making using a systems approach to the delivery of health care. A patient-centred focus is essential to ensure the health care and social needs of the population are adequately met [5,7].

The CN process evaluation provides qualitative data to complement outcome measures collected by the trial. If significant changes in patient and health service outcomes are observed, the process evaluation describes the mechanisms underpinning these changes. An account of the implementation of the intervention, and the context of the health system it is conducted within, gives a richer understanding of the intervention and enhances the external validity of the RCT.

The design of the RCT incorporates a large sample size with adequate power to detect the primary outcomes, and a long follow-up period to observe meaningful improvements in patient health outcomes [18,19]. The use of independent random assignment to the intervention, blinding where feasible, and an intention to treat analysis minimises bias.

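### The power of over 90% for hospital admissions holds only with near-Poisson variance; the sample size states no allowance for overdispersion

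*Protocol article*

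**What the plan says.** All places are in the protocol article.

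- **Study size.** The recruitment target is 500. On attrition the section says: "With an expected 20% loss to follow-up, this results in a final sample size of 400". It then describes that number as "giving over 90% power to detect a 20% reduction in hospital admissions at a 5% significance level". The assumed effect is set out in these words: "This effect size is a rate ratio of 0.8 based on an average of 2.5 admissions per patient over a two year period". That mean belongs to the control arm; the intervention arm is put at 2.0. Only means are given. No standard deviation, variance or dispersion of the counts appears here or elsewhere in the article, and the test is not said to be one- or two-sided.
- **Consent and randomisation.** "Randomisation is 1:1 allocation and is conducted using permuted block design", so 400 analysed patients means 200 per arm.
- **Statistical analysis.** "Readmission rates and length of stay are analysed using Poisson or Negative Binomial models". Model checking and goodness-of-fit tests are also promised for all analyses.
- **Study variables.** The hospital re-admission rate is one of three primary outcomes.
- **Discussion.** "The design of the RCT incorporates a large sample size with adequate power to detect the primary outcomes". The same section presents the trial as taking in mixed patient groups whose illnesses differ in kind and severity. It also says that consent is obtained at baseline to collect hospital data electronically for the whole follow-up.

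**The concern.** Admission counts in a chronically ill population usually vary between patients by more than a Poisson distribution allows. This article gives reasons to expect that. The entry routes are diverse: age 70 or over, Aboriginal or Torres Strait Islander patients from age 45, and patients from age 16 with a respiratory or cardiology admission. A further route, clinician recommendation, carries no admission threshold. The analysis section also names a negative binomial model, whose purpose is to handle such extra variation.

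The sample size gives two means and a power figure, with nothing on variation. If the figure comes from a Poisson calculation, the planned analysis foresees overdispersion and the power claim leaves it out. What is at stake is how a null result on a primary outcome is read. A reader who trusts the 90% figure and the Discussion's statement of adequate power would take a null result as fairly strong evidence against a 20% reduction. At lower power it would be weaker evidence.

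**Working it through.** **Inputs.** Control mean 2.5, intervention mean 2.0, rate ratio 0.8, 5% level, 400 analysed of 500 recruited (Study size); 1:1 allocation (Consent and randomisation). A two-sided test is assumed because the article does not say. The dispersion k is an assumption throughout, because the documents give none.

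**Formula.** For negative binomial counts with variance μ + kμ², and n patients per arm:

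- Var(log RR) = (1/2.5 + 1/2.0 + 2k)/n = (0.9 + 2k)/n
- Power = Φ(|ln 0.8|/SE − 1.96), with |ln 0.8| = 0.2231

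k = 0 is the Poisson case.

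**Step 1: reproduce the plan's figure.** With n = 200 and k = 0, Var = 0.9/200 = 0.0045, SE = 0.0671, and 0.2231/0.0671 = 3.33. Power = Φ(3.33 − 1.96) = 91.4%. Working on the rate difference gives 91.5%, and on the square-root scale 91.6%. So the stated figure is reproduced under Poisson variance, with a margin of about 1.4 points over 90%.

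**Step 2: how much overdispersion the figure tolerates.** Setting power to a target and solving for k:

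k = ½ [ n (0.2231/(1.96 + z))² − 0.9 ], with z = 1.282 for 90% and 0.842 for 80%.

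| Analysed | k at which power is 90% | k at which power is 80% |
|---|---|---|
| 400 (n = 200) | 0.024 | 0.18 |
| 500 (n = 250) | 0.14 | 0.34 |

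The control-group variance-to-mean ratio is 1 + 2.5k. With 400 patients it is about 1.06 at the 90% limit and 1.46 at the 80% limit.

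**Step 3: power over an assumed range of k.**

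| Assumed k | Control variance/mean | SE, n = 200 | Power, 400 | Power, 500 |
|---|---|---|---|---|
| 0 | 1.00 | 0.0671 | 91.4% | 96.1% |
| 0.10 | 1.25 | 0.0742 | 85.3% | 92.0% |
| 0.25 | 1.63 | 0.0837 | 76.0% | 84.7% |
| 0.50 | 2.25 | 0.0975 | 62.9% | 72.6% |
| 1.00 | 3.50 | 0.1204 | 45.7% | 54.5% |
| 1.50 | 4.75 | 0.1396 | 35.9% | 43.1% |

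A simulation with 1,000 fitted negative binomial models per value of k, 200 per arm, gave 74.6% (k = 0.25), 63.3% (k = 0.5), 44.6% (k = 1) and 35.8% (k = 1.5), in line with the formula. At k = 0 the simulated Poisson power was 93.3%, slightly above the formula, so the limit of 0.024 is approximate.

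**Step 4: rate ratio detectable with 80% power.** Solve |ln RR| = (1.96 + 0.842) × √[(1/2.5 + 1/(2.5·RR) + 2k)/n]. For n = 200 this gives about 0.76 at k = 0.5 and 0.71 at k = 1. As a check at k = 0.5: with RR = 0.76 the variance is (0.4 + 0.526 + 1)/200 = 0.00963, SE = 0.0981, and 2.802 × 0.0981 = 0.275 = −ln 0.76. For n = 250 the same equation gives about 0.78 and 0.74.

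**The case against.** Several parts of the opposing case stand.

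- **The range is assumed.** A reader might infer that the trial's power under a negative binomial model simply is 46% to 76%. The documents do not support that. Those figures belong to k = 0.25 to 1 with 400 patients. The same model gives 85% at k = 0.10 and 36% at k = 1.5. The article's description of its patients is qualitative and fixes no value of k.
- **Some overdispersion is tolerable.** It would be too strong to say that the claim requires no between-patient variation at all. It survives up to k of about 0.024 with 400 patients. A one-sided test, which the article neither states nor rules out, would extend this to about 0.13.
- **All 500 may be analysed for admissions.** Table 1 lists admissions as an electronic report, and the Discussion describes electronic capture for the whole follow-up. The 20% loss may therefore affect the telephone questionnaire far more than the admission counts. This is a fair point, and both sample sizes belong in the restatement. It does not rescue the claim at k = 0.25 or above, where power with 500 is 85% or less. The article also attaches its figure to 400.
- **The control mean may be conservative.** The algorithm requires three or more admissions in 12 months, so 2.5 over two years may be low. With an assumed mean of 5, power with 400 patients would be about 90% at k = 0.25 and 75% at k = 0.5. This limits any forecast of actual power, but does not support the figure stated for 2.5.
- **False positives.** A reader might also infer that the 5% level is broken because plain Poisson is listed. The plan does not support this. It pairs Poisson with negative binomial and commits to checking model fit. The choice of one model and its offset is detail that an article commonly leaves to the analysis plan.

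**Conclusion.** The point holds as a statement about an unstated assumption. The 90% figure is not an arithmetic slip: it reproduces at 91.4%, but only with essentially Poisson variance. With 400 patients and a two-sided test, a control variance-to-mean ratio of about 1.06 is enough to lose it. The plan's own choice of models and its description of the patients make an allowance for overdispersion necessary, and none is stated.

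The size of the shortfall is unknown, because the documents do not give k. Over the assumed range of 0.25 to 1, the loss from the reproduced 91.4% is about 15 to 46 points with 400 patients. With 500 analysed, the same range leaves power about 5 to 36 points below the claimed 90%. These results rest on the article's means and rate ratio, a two-sided 5% test, a common k in both arms and full two-year exposure for each analysed patient. The documents do not show that the trial is in fact underpowered; they show that the stated figure is unsupported unless k is close to zero.

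**What to change.** 1. In Study size, state the dispersion assumption behind the admissions figure and whether the test is one- or two-sided.
2. Restate power for hospital admissions under a negative binomial model over a range of k labelled as assumed, for both 400 and 500 analysed patients. Give the rate ratio detectable with 80% power beside it (about 0.76 at k = 0.5 and 0.71 at k = 1 with 400 patients).
3. Where possible, take k from existing hospital records of patients who meet the inclusion algorithm, or from blinded pooled trial data, so that the allocation stays masked.
4. Qualify the Discussion's statement of adequate power so that it matches the restated figures.

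This is a change of wording plus a short calculation. It needs no extra patients and no change to trial conduct. The cost is a less favourable stated power.

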### Statistical analysis

Cox proportional hazards models are used to analyse time to first ED presentation, time to first readmission and time to mortality. Readmission rates and length of stay are analysed using Poisson or Negative Binomial models. EQ-5D is analysed using analysis of variance, and t-tests for pairwise comparisons. Baseline characteristics, such as age, gender and severity of illness are examined. Model checking of assumptions and good-of fit tests are conducted for all analyses and further analyses are conducted as required. All analyses are conducted according to the intention-to-treat principle, and will be conducted in SAS v9.3.

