### Study variables

In addition to the inclusion and exclusion criteria, six types of variables are collected: demographic and other risk factors, psychosocial, hospital utilisation, community health utilisation, medication usage, and mortality variables. Outcome variables are calculated after 12 months and/or 24 months of follow-up period (Table 1).

**Table 1 T1:** Quantitative data collected in the Care Navigation randomised controlled trial

**Type of data**	**Variables**	**Data source**	**Time of data collection**
**Demographic and risk factor variables**	Age, sex, Indigenous status, marital status	Electronic report from NSW Health database	Baseline.
	Literacy, language, ethnicity, income, education, BMI, living arrangements smoking, alcohol, physical and mental disability, comorbidities	Phone questionnaire-manual data entry	12 months.
**Psychosocial variables**	Quality of life: EQ-5D questionnaire [16]	Phone questionnaire-manual data entry	Baseline, 12 months, 24 months.
	Patient experience: Picker patient experience questionnaire [18]	Mailed paper questionnaire-manual data entry	12 months.
**Hospital utilisation variables**	*For each emergency presentation within the follow-up period:* Triage category, arrival date and time, departure date and time, mode of separation, presenting problem and diagnosis, UDAG status	Electronic report from NSW Health database	24 months.
	*For each hospital admission within the follow-up period:* Arrival date and time, departure date and time, diagnosis related group (DRG), service related group (SRG), investigations conducted	Electronic report from NSW Health database	24 months.
**Community health utilisation variables**	*For each community referral within the follow-up period:* Referral service type, appointment date and time, treatment administered, attendance and transport	Electronic report from NSW Health database	24 months.
**Medication utilisation variables**	Clinical service utilisation (MBS)	Electronic report from Statistics Medicare Australia	24 months.
	Pharmaceutical utilisation (PBS)	Phone questionnaire (manual data entry)	Baseline, 12 months, 24 months.
	Adherence to medications [19]		
**Mortality data**	Date of death	Electronic report from the National Death Index (Australian Institute of Health and Welfare)	24 months.

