The three primary outcome measures are a) the rate of re-presentations* to the emergency department; b) the rate of hospital re-admissions*, and c) quality of life. Secondary outcome measures are the length of hospital stay, mortality rates, time to first hospital re-admission, time to first ED re-presentation, hospital key performance indicators, patient satisfaction, and adherence to prescribed medications.

*Includes presentations and admissions to any Western Sydney or Nepean Blue Mountains Local Health District hospital.

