The main challenges of the intervention are loss to follow-up, heterogeneity of the intervention received between patients, and bias in patient recruitment. Loss to follow-up is minimised by receiving consent at baseline for hospital, medication and death data to be obtained electronically from local and national health databases for the entire follow-up period. Patients are also in regular contact with CN nurses during the period of follow-up to action care plans, however, follow-up data collection is not conducted by CN nurses to minimise bias. The intervention is conducted with consistent protocols to minimise between-patient variability. Care Navigation nurses are trained in these protocols, and intervention delivery checklists are used to record intervention delivery to the patients. To minimise bias in patient recruitment, eligibility criteria are designed to capture all patients who would normally receive CN upon presentation to the emergency department, while still maintaining accuracy and completeness of the data. Efforts are made to accommodate culturally and linguistically diverse patients.

This mixed-methods study informs the generalisability and sustainability of care coordination programs in Australia and internationally. The CN trial aims to build upon these principles to provide a comprehensive coordinated care program for improving health outcomes among patients with chronic illness.

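### The EQ-5D, a primary outcome, is to be analysed by ANOVA and t-tests that do not use the collected baseline EQ-5D as a covariate, so precision is given up

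*Protocol article*

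**What the plan says.** The Study variables section makes quality of life the third primary outcome, beside the rates of emergency re-presentation and hospital re-admission. Table 1 names the EQ-5D, asked by telephone, as the instrument and gives its timing as "Baseline, 12 months, 24 months".

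The Statistical analysis section gives this outcome one sentence: "EQ-5D is analysed using analysis of variance, and t-tests for pairwise comparisons". On baseline data it adds: "Baseline characteristics, such as age, gender and severity of illness are examined". It does not name baseline EQ-5D as a covariate. It does not say how the 12- and 24-month values enter the analysis, or which of them is primary. It also states: "All analyses are conducted according to the intention-to-treat principle".

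The Study size section plans for 400 analysed out of 500 recruited. It says that this number would allow the trial to "detect a mean difference of 10 points on the EQ-5D scale [16], with approximately 80% power at a 5% significance level". Allocation is 1:1, stratified by an age grouping (Consent and randomisation section).

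**The concern.** A patient's own baseline score is usually the strongest single predictor of a later quality-of-life score, and here it is collected anyway. The participants are deliberately mixed in age, diagnosis and severity, so much of the spread in follow-up scores may be spread that was already present at entry. Conditioning on baseline removes that part from the error term and also corrects for chance imbalance between the arms. A t-test or ANOVA on follow-up scores does neither.

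This matters most for the EQ-5D because its margin is the thinnest of the three primary outcomes. The Study size section claims over 90% power for admissions and more than 80% for emergency re-presentations, but only about 80% for the EQ-5D.

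**Working it through.** **Inputs from the article.** 400 analysed, 1:1, so 200 per arm; difference 10 points; power about 80%; significance level 5%.

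**Assumptions.** Two-sided test (sidedness is not stated). The stated 80% belongs to an unadjusted comparison of follow-up scores. The baseline to follow-up correlation r is not given, and a range of 0.3 to 0.7 is used. The standard deviation (SD) is the same at baseline and follow-up.

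**The plan's own figure.** No EQ-5D SD is given, so the 80% cannot be reproduced. It can only be solved backwards:

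SD = 10 / [(1.960 + 0.842) × √(2/200)] = 10 / (2.802 × 0.1) = 35.7 points.

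In other words, the stated power fixes the ratio of the difference to its standard error at 2.802.

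**Effect of baseline adjustment.** ANCOVA has residual SD = SD × √(1 − r²), so

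power = Φ(2.802 / √(1 − r²) − 1.960).

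A change-score analysis has SD × √(2(1 − r)), so

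power = Φ(2.802 / √(2(1 − r)) − 1.960).

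The difference detectable with 80% power under ANCOVA is 10 × √(1 − r²).

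| r | 1 − r² | Unadjusted | Change score | ANCOVA | Detectable difference, ANCOVA |
|---|---|---|---|---|---|
| 0.3 | 0.91 | 80% | 65.8% | 83.6% | 9.5 points |
| 0.4 | 0.84 | 80% | 72.5% | 86.4% | 9.2 points |
| 0.5 | 0.75 | 80% | 80.0% | 89.9% | 8.7 points |
| 0.6 | 0.64 | 80% | 87.9% | 93.8% | 8.0 points |
| 0.7 | 0.51 | 80% | 95.1% | 97.5% | 7.1 points |

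Worked line for r = 0.5: 2.802 / √0.75 = 3.235; 3.235 − 1.960 = 1.275; Φ(1.275) = 89.9%.

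ANCOVA gains about 4 to 18 percentage points over the unadjusted test. It is above the change-score analysis in every row. Below r = 0.5 the change score does worse than ignoring baseline altogether.

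**What a mixed model adds to ANCOVA.** As an illustration, suppose that 200 per arm are seen at both follow-ups and another 25 per arm at 12 months only. Conditional on baseline, the two follow-up values have variance SD²(1 − r²) and covariance SD²(f − r²), where f is the correlation between the follow-ups. Call this 2 × 2 matrix C. The information per arm is 200 × C⁻¹, plus 25/C₁₁ in the 12-month entry. The variance of the 24-month arm difference is twice the 24-month entry of the inverse.

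| r | f | Complete-case ANCOVA | Mixed model |
|---|---|---|---|
| 0.3 | 0.4 | 83.6% | 84.0% |
| 0.5 | 0.6 | 89.9% | 90.6% |
| 0.6 | 0.7 | 93.8% | 94.5% |

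The extra power is under one percentage point. Nearly all the gain comes from the baseline covariate.

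**The case against.** **The unadjusted test is sound.** In a 1:1 randomised trial it keeps its type I error rate, which already allows for chance imbalance. The article claims its 80% without relying on adjustment. This stands: the point concerns efficiency only.

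**The size is assumed.** The article supports no value of r, and the SD is solved backwards. At r = 0.3 the gain is only about 4 points. This also stands, and it is why a range is shown. The direction does not depend on the range: any non-zero correlation favours adjustment.

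**The sentence is condensed and may mean something else.** With two arms at one visit, ANOVA and the t-test are the same test. Naming both, with pairwise comparisons, may point to an arm-by-time model that includes the baseline visit. That is possible. In such a model the arm-by-time contrast with baseline compares changes, so the change-score column applies, and it is below ANCOVA throughout. The charitable reading narrows the point without removing it.

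**Stronger readings that the article does not support.** A reader might infer that the plan drops every patient without a follow-up score. The article never says so. The 400 of 500 is a planning allowance, and missing-data rules are commonly left to a fuller document that is not shown. Nor would such a loss follow from ignoring baseline, because ANCOVA on complete cases loses the same patients.

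A reader might also infer unequal retention, or nurses prompting questionnaires, from the Discussion's remark: "Patients are also in regular contact with CN nurses during the period of follow-up to action care plans". The same sentence goes on to say that these nurses do not collect follow-up data, and the Consent and randomisation section assigns collection to a blinded research assistant. Nurse contact could still affect retention, but the article gives no figure from which to argue it.

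**Conclusion.** The point holds as a matter of efficiency. The only analysis named for a primary outcome does not condition on a baseline measure that the trial collects. Taking the stated 80% as the unadjusted power, adjustment would bring it to about 84% at r = 0.3, 90% at r = 0.5 and 98% at r = 0.7. If the true SD differs from the implied 35.7, all these powers shift together, but ANCOVA remains the most powerful of the three analyses.

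Confidence is high that a baseline-adjusted model is at least as precise as what is named, and only moderate about how much is lost, since both r and the exact meaning of the ANOVA sentence are uncertain. The change is worth making. Without it the trial's inference on the EQ-5D is still valid.

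**What to change.** In the Statistical analysis section, replace the ANOVA and pairwise t-tests with one baseline-adjusted model for the EQ-5D. Two forms would serve:

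- ANCOVA at the primary time point, with baseline EQ-5D and the randomisation stratum as covariates.
- A mixed model for repeated measures on the 12- and 24-month values, with arm by visit, baseline EQ-5D by visit, the randomisation stratum and an unstructured within-patient covariance.

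Either way, state whether 12 or 24 months is the primary comparison.

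The mixed model also uses patients seen at 12 but not at 24 months. This adds little power and mainly guards against bias. It must come with a statement on deaths: mortality is itself a secondary outcome over 24 months in a severely ill group, and the model would otherwise treat scores after death as missing values to be inferred from the survivors.

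The cost is a few sentences of text and two decisions, the primary time point and the handling of deaths. No new data, visits or patients are needed.
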